### Data analyses

As this is a pilot study, significance tests of change over time will not be performed on the primary of secondary outcomes. Intervention effects will be represented by point estimates, and both 85 and 95% confidence intervals will be estimated at each follow-up time point [55]. Analysis will be conducted by a researcher blind to group allocations. Recruitment, retention and adherence rates will be reported and any adverse events recorded and, alongside effect size, will be used to estimate a sample size required for a definitive trial, if deemed appropriate. All semi-structured interviews and focus groups will be audio-recorded and transcribed verbatim for further analysis. Transcripts from audio recordings will be analysed using standard thematic analysis techniques [36]. At least two qualitative researchers will structure the data and subsequent interpretation. Themes will be compared to the results of the post-study exit questionnaires to make a judgement about the overall acceptability of the intervention.

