**Methods:**

The Medical Research Council framework for developing and evaluating complex interventions will be used to design and test the feasibility of a randomised controlled trial (RCT) of a multicomponent peer-led physical activity intervention. Data will be collected at baseline, immediately after the intervention (12 weeks) and 6 months after baseline measures. The pilot RCT will provide information on recruitment of peer mentors and participants and attrition rates, intervention fidelity, and data on the variability of the primary outcome (minutes of moderate to vigorous physical activity measured with an accelerometer). The pilot trail will also assess the acceptability of the intervention and identify potential resources needed to undertake a definitive study. Data analyses will be descriptive and include an evaluation of eligibility, recruitment, and retention rates. The findings will be used to estimate the sample size required for a definitive trial. A detailed process evaluation using qualitative and quantitative methods will be conducted with a variety of stakeholders to identify areas of success and necessary improvements.

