### Study design and setting

Using the Medical Research Council (MRC) framework for complex interventions [26], we designed a multilevel peer-led physical activity intervention for older adults, tailored to meet the needs of the local community. The intervention package has been developed after defining appropriate BCTs for inclusion in the intervention. They were used to inform the intervention design by (i) identifying BCTs used in previous peer-led interventions. To identify BCTs employed in previous peer-led interventions, a rapid review of the literature was conducted and the use of BCTs was extracted; (ii) conducting interviews with members of the target population to explore their preferences for, and the perceived feasibility of particular BCTs identified from the rapid review. Based on the outcome of these stages, we will then (iii) conduct a pilot randomised controlled trial (RCT). The trial will provide information on recruitment and attrition rates, intervention fidelity, data on the variability in objective physical activity measurements and the resources needed to support the development of a definitive trial [27].

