#### Phase 3: pilot RCT

The aim of the trial is to test the feasibility of conducting a trial of a peer-led walking programme in promoting sustained increases in objectively measured physical activity in order to enhance health and mental wellbeing, increase social engagement and improve quality of life in community dwelling older adults.

We will conduct a pilot RCT with 60 inactive, community-dwelling older adults aged 60–70 years, residing in socio-economically disadvantaged communities. In their seventh decade, adults from socio-economically disadvantaged areas often transition from good health to poor health, from being fit to being unfit, from independence to dependence and may transition from employment to retirement [37]. This age range (60–70 years) therefore can be seen as a transition period, as older adults from socio-economically disadvantaged areas transition from good health to poor health.

Physical activity interventions delivered at points of life transition such as changes in social (loss of companions), economic (retirement) or health circumstances in older adults may be advantageous. Li et al. [37] acknowledged that this ‘transition’ is not necessarily an abrupt change, but may involve a gradual change over time. Whilst retirement from paid employment may lead to change in employment and income, these transitions may not be applicable to many people in disadvantaged communities. Thus, in addressing the identified research priorities of inequalities in health and physical activity participation in socio-economically disadvantaged communities, we will include all 60–70-year-olds in such communities in our target population rather than focusing on retirement.

For this study, socio-economically disadvantaged communities are defined as those falling within the lowest quartile of super output areas (geographical areas of consistent size used to facilitate the calculation on deprivation indices), based on the Northern Ireland Multiple Deprivation Measure (NIMDM) (https://www.nisra.gov.uk/). For ease of administration, the pilot study will be conducted in the South-Eastern and Northern Health & Social Care Trusts, which covers a large geographical area and a mix of urban and rural settings. In doing so, the intervention would fill an identified gap in preventive service provision for older adults who may need support to increase their physical activity levels in order to maintain physical function and independence in daily living.

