#### Allocation and randomisation

After contacting the study team, potential participants’ meet with a member of the project team to discuss the study in detail. At this face to face contact, all eligible participants are informed about the details of the project, including what the intervention and the control group will receive and what outcomes are collected. They are advised that participation in the project is voluntary and that they have the right to withdraw consent, at any time, without the need for explanation. They are given a minimum of 48 h to consider participation in the study. After this, those who wish to take part are asked to read, complete and sign a consent form, which will be returned to, and countersigned by a member of the research team. Eligible participants complete baseline outcome measures and are then randomised to an intervention or control group (1:1 ratio) using block randomisation with randomly permuted block sizes. The Northern Ireland Clinical Trials Unit (NICTU) trial statistician will generate the randomisation sequence which will be concealed in sealed envelopes opened by a member of the research team responsible for pairing the mentors and intervention group participants, after completion of baseline measures.

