### Outcome measures

Outcome measures will be assessed at baseline (prior to randomisation), after completing the intervention (12 weeks) and 6 months after baseline (Table 2). All outcomes have been chosen in order to inform the development of a future definitive trial. We plan to assess the feasibility and acceptability of employing these measures.

**Table 2 Tab2:** Outcome measures and time points in the Walk with Me trial

Outcome	Measurement tool	Time points
MVPA	GT3X+ accelerometer	Baseline, 12 weeks, 6 months
Self-reported physical activity	EPAQ-2	Baseline, 12 weeks, 6 months
Physical and mental health	SF-12	Baseline, 12 weeks, 6 months
Mental wellbeing	Warwick-Edinburgh Mental Well-being Scale	Baseline, 12 weeks, 6 months
Health-related quality of life	EuroQol-5D	Baseline, 12 weeks, 6 months
Loneliness	UCLA Loneliness Scale	Baseline, 12 weeks, 6 months
Social engagement	Lubben Social Network Scale	Baseline, 12 weeks, 6 months
Health and social care services resource use	Annotated Cost Questionnaire	Baseline, 12 weeks, 6 months
Acceptability of the intervention	Post-intervention exit questionnaire	6 months
Self-efficacy	Physical Activity Self-Efficacy Measure [49] Social Activity Self-Efficacy Measure (adapted from [49])	Baseline, 12 weeks, 6 months
Outcome expectancies	Physical Activity Outcome Expectancy Measure (Items 1–12 from [50]) Social Activity Outcome Expectancy Measure (Adapted from [50])	Baseline, 12 weeks, 6 months

The primary outcome measure will be mean daily minutes of moderate and vigorous physical activity (MVPA) objectively measured over 7 days using a waist-worn Actigraph GT3X+ accelerometer. Participants will be asked to wear the accelerometer on an elasticated belt, during waking hours, for seven consecutive days. To explore the context of changes in physical activity and the types of physical activity that participants report performing, a validated self-reported physical activity questionnaire (EPAQ-2) [41] will be self-completed.

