### Process evaluation

In line with MRC guidance on process evaluation [51], we will assess whether the intervention was delivered and received as intended (implementation), how intervention activities, and participants’ interactions with them impacted behaviour change (mechanisms of impact; through behavioural processes as per logic model––Fig. 2); and how potential external factors may have influenced the delivery and functioning of the intervention (context; through post-intervention focus groups).

Process evaluation will assess whether the intervention was delivered and received as intended. This will be achieved through structured observation of intervention delivery (by a member of the research team responsible for mentor training), semi-structured interviews and focus groups with peer mentors and participants, and review of intervention records and participant diaries.

Intervention implementation fidelity will be assessed in the following ways. For each peer mentor, one randomly selected first meeting and follow-up meeting will be audio-recorded and assessed by the research team for content and delivery fidelity, using a quality assurance form.

Feedback on fidelity will be given to each peer mentor during the intervention to assist them in delivery. Completeness in the dose of delivery of the intervention will be assessed by asking the peer mentors and a sample of 10 trial participants to complete weekly checklists and record a diary of contacts (both face-to-face and telephone). The diary will include information on the number of attempts to make contact and the duration of each successful contact. This information will be summarised at the end of the intervention in line with the studies fidelity assessment and implementation plan [52] to assess overall fidelity.

To assess theoretical mediators of physical activity behaviour (mechanisms of impact), physical activity and social activity self-efficacy and physical activity and social activity outcome expectancies will be measured (see study logic model––Fig. 2).

Post-intervention focus groups and semi-structured interviews will be used to provide context to the research by examining how potential external factors may have influenced the delivery and functioning of the intervention.

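### The pilot's observed effect size is to feed the definitive trial's sample size, but 60 participants estimate it too imprecisely and no important difference is named

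*Protocol article*

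**What the plan says.** The article describes a pilot: "We will conduct a pilot RCT with 60 inactive, community-dwelling older adults aged 60–70 years", "randomised to an intervention or control group (1:1 ratio) using block randomisation with randomly permuted block sizes". The outcome at issue is continuous: "The primary outcome measure will be mean daily minutes of moderate and vigorous physical activity (MVPA) objectively measured over 7 days".

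Two places say what the pilot should supply for the next trial. The abstract's Methods paragraph promises "data on the variability of the primary outcome" and adds that the findings will be used to estimate the definitive sample size. Study design and setting promises "data on the variability in objective physical activity measurements and the resources needed to support the development of a definitive trial". Both name variability, and neither names the treatment effect.

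The Data analyses section differs. It rules out significance tests because this is a pilot, then states: "Intervention effects will be represented by point estimates, and both 85 and 95% confidence intervals will be estimated at each follow-up time point". It goes on to say that recruitment, retention and adherence rates and adverse events, "alongside effect size, will be used to estimate a sample size required for a definitive trial, if deemed appropriate". That sentence does not mention the SD of MVPA. The article gives no important difference, SD, alpha or power for the definitive trial.

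**The concern.** A definitive sample size needs a target difference that would matter, plus nuisance quantities such as the SD and the loss to follow-up. A pilot can inform the nuisance quantities tolerably well. It cannot locate the effect, and the required size varies with the inverse square of the effect, so moderate error in the estimate becomes very large error in N.

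The section declines to test the pilot's effect but lets the same estimate drive the next trial's size. Because the abstract makes that size a declared output, what is at stake is a definitive trial that is far too small, far larger than needed, or impossible to size because the estimate is zero or points the wrong way.

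**Working it through.** The article gives no definitive sample size, so there is no figure to reproduce.

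**Inputs from the article:** 60 randomised 1:1, so 30 per arm; a continuous primary outcome; effect size as an input to the definitive size.

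**Assumptions, because the article gives no values:** 30 analysed per arm (no loss) or 24 per arm (20% loss); true standardised effect d from 0.2 to 0.5; two-sided alpha 0.05; 90% power target; comparison not adjusted for baseline.

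**1. Precision of the pilot effect.** SE(d) ≈ √(2/n).
- 30 per arm: √(2/30) = 0.258; 95% half-width 1.96 × 0.258 = 0.51; 85% half-width 0.37.
- 24 per arm: √(2/24) = 0.289; 95% half-width 0.57; 85% half-width 0.42.

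**2. What this does to N.** N per arm = 2 × ((1.96 + 1.2816)/d)². At true d = 0.30 the need is 233.5, so 234 per arm. With 24 per arm, the middle half of pilot estimates is 0.30 ± 0.6745 × 0.289, that is 0.105 to 0.495.
- An estimate of 0.105 gives about 1,900 per arm, roughly eight times the need.
- An estimate of 0.495 gives 86 per arm. True power is then Φ(0.30 × √(86/2) − 1.96) = Φ(0.007), about 50%.

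**3. Average consequence.** For each scenario, 1,000,000 pilot estimates were simulated (noncentral t). The definitive trial was sized from each with the formula above, and its power computed at the true d. Without selection, the absolute value of the estimate was used, so that a size always exists. Under-sized means N below the N needed for the true d.

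| Analysed per arm | True d | N needed per arm | Mean power, no selection | Mean power, estimate > 0 | Estimate ≤ 0 | Under-sized, no selection | Under-sized, estimate > 0 |
|---|---|---|---|---|---|---|---|
| 30 | 0.2 | 526 | 69.4% | 64.1% | 21.9% | 56.3% | 64.2% |
| 30 | 0.3 | 234 | 75.9% | 73.0% | 12.2% | 51.2% | 57.2% |
| 30 | 0.4 | 132 | 79.3% | 78.0% | 6.0% | 50.3% | 53.4% |
| 30 | 0.5 | 85 | 81.4% | 80.9% | 2.6% | 50.3% | 51.7% |
| 24 | 0.2 | 526 | 66.9% | 61.2% | 24.4% | 58.4% | 66.2% |
| 24 | 0.3 | 234 | 74.4% | 70.7% | 14.9% | 52.1% | 58.9% |
| 24 | 0.4 | 132 | 78.1% | 76.2% | 8.3% | 50.4% | 54.6% |
| 24 | 0.5 | 85 | 80.3% | 79.5% | 4.2% | 50.3% | 52.5% |

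Mean power misses 90% in every row. Over-sizing cannot make up for under-sizing, because power cannot exceed 100%.

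**4. Comparison with the proposed use of the pilot.** Fix the target difference in advance and take only the SD from the pilot (true d = 0.3 equal to the target difference, 80% power target).
- 30 per arm: power falls below 70% in 12% of pilots, against 45% when sizing on the observed effect.
- 24 per arm: 15% against 46%.

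The SD is the better-determined quantity. Its 95% interval runs from 0.85 to 1.22 times the estimate with 30 per arm, and from 0.83 to 1.26 with 24.

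**The case against.** The strongest reply is that little harm is done. The stated objectives concern mentors and feasibility. Randomisation, data collection and the pilot's own estimates are unaffected. The 85% and 95% intervals will show the imprecision, the sentence is conditional, and the inputs can still be chosen when the definitive trial is designed. This stands as an argument about severity. It does not rescue the rule, because the article states an unsuitable input for a declared output.

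Three stronger readings are tempting and are not supported.

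- **That the definitive trial would usually be too small.** The pilot estimate is nearly unbiased. Without selection, under-sizing occurs in 50% to 52% of pilots at d = 0.3 to 0.5 and in 56% to 58% at d = 0.2. Median power at d = 0.4 to 0.5 is about 90%, on target. Under-sizing becomes clearly more likely than not if the trial goes ahead only after a favourable estimate: at d = 0.3 and a threshold of 0.2, it occurs in 77% to 79%. The article sets no such filter. The section on feasibility and acceptability judges feasibility on recruitment, attrition and qualitative feedback.
- **That using the raw pilot SD adds a second under-sizing.** A standardised effect already contains the SD. With SD-only sizing at 30 per arm, median power is 79.7% against an 80% target. An upper confidence limit for the SD is an optional safety margin.
- **That clustering by mentor is ignored.** The Process evaluation section ("For each peer mentor, one randomly selected first meeting and follow-up meeting will be audio-recorded") hints that a mentor may have several participants, but other sections speak of pairing and no ratio is given. Any cluster size or intraclass correlation would be a guess about a calculation that the article does not set out.

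**Conclusion.** The point holds in a limited form. The Data analyses section names the pilot's effect size as an input to the definitive sample size, and about 60 participants cannot estimate it well enough for that purpose. The error runs in both directions. Against an assumed 90% target, mean true power is about 67% to 81% with no selection, and about 61% to 81% if only positive estimates can be used. In about 3% to 24% of pilots the estimate is zero or negative and gives no sensible size.

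These figures rest on assumed true effects of 0.2 to 0.5 SD, 24 or 30 analysed per arm and an unadjusted comparison. Adjustment for baseline would act like a move to a larger d in the table. The shortfall in mean power appears in every scenario, and its size depends on the unknown true effect. Reading effect size as the observed estimate is an inference, but a natural one: the same paragraph presents effects as point estimates, and no other difference is named.

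This is a worthwhile correction to a stated rule. It does not threaten the validity of the pilot.

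**What to change.** In Data analyses, delete the phrase that makes effect size an input. State instead that the definitive trial will be sized on a minimum important difference in mean daily MVPA minutes, fixed before the pilot results are known.

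Take from the pilot:
- the SD of MVPA, with its uncertainty shown;
- the correlation between baseline and follow-up MVPA;
- the share of randomised participants without valid follow-up MVPA.

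Keep the pilot effect with its 85% and 95% intervals, and use it only to check that the important difference is not ruled out.

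The cost is about two sentences and no new data. The team must agree and justify an important difference, and the definitive sample size may turn out less favourable than one built on a lucky pilot estimate.

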## Discussion

This study focuses on the need to address declining levels of physical activity in the older adult population. The Walk with Me trial aims to test the feasibility of a theory-based peer-led intervention to increase the physical activity of inactive community-dwelling older adults from areas of socio-economic deprivation. The study design and evaluation was informed by the MRC framework for complex interventions, and is based on extensive prior development work, including a systematic review and semi-structured interviews with members of the target population. In addition, the emphasis is on rigorous evaluation using objective and self-reported outcome and process measures. The data collected in this pilot trial will inform the design and delivery of a fully powered definitive trial if deemed appropriate.

## Abbreviations

BCT: Behaviour Change Technique
GHQ: General Health Questionnaire
MRC: Medical Research Council
MVPA: Moderate to Vigorous Physical Activity
NICTU: Northern Ireland Clinical Trials Unit
NIHR: National Institute of Health Research
NIMDM: Northern Ireland Multiple Deprivation Measure
RCT: Randomised controlled trial
SCT: Social cognitive theory
SF-12: Short-Form 12
